**Mental health**	
**Psychiatric care**	Must have a psychiatrist and/or general practitioner who is able to provide psychiatric follow-up care
**Diagnosis**	Have a Mini International Neuropsychiatric Interview (MINI)-confirmed diagnosis of a depressive disorder, recurrent or single episode, without psychotic features where the duration of the current episode is at least 3 months Depression of at least moderate severity as defined by a Hamilton Depression Rating Scale (HAMD-17) score of greater than 17
	**Exclusion criteria**
**Physiological health**	
**Medical History**	Uncontrolled or insulin-dependent diabetes Women who are pregnant (self-report or via urine test), nursing, or planning a pregnancy during the timespan of the study History of seizure disorder except for seizures from electroconvulsive therapy and/or febrile seizures in childhood History of stroke, recent myocardial infarction (< 1 year from signing of ICF), uncontrolled hypertension (blood pressure > 140/90 mmHg) or clinically significant arrhythmia within 1 year of signing the ICF Any other clinically significant cardiovascular, pulmonary, gastrointestinal, hepatic, renal or any other major concurrent illness that, in the opinion of the investigator, may interfere with the interpretation of the study results or constitute a health risk for the participant if he/she takes part in the study
**Vital signs**	Abnormal and clinically significant results on a physical examination performed within one month of study participation by a general practitioner, vital signs, ECG, or laboratory test at screening QTc prolongation on ECG defined by > 450 ms in males and > 460 ms in females in V_5_ on a 12-lead ECG [88]
**Lab work**	Positive urine drug screen for illicit drugs or drugs of abuse at screening, a week prior to treatment, and during the trial (any positive urine drug test will be reviewed with participants to determine the pattern of use and eligibility will be determined at the investigator’s discretion) Serial blood counts to achieve a value to meet eligibility — abnormalities in screening/baseline blood work (complete blood counts, electrolyte panel, etc.) will be reviewed by MD, then repeated serially until abnormalities resolve
**Mental health**	
**Current risk**	Any symptoms consistent with psychosis Any symptoms consistent with hypomania and/or mania as assessed by a psychiatrist Other personal circumstances or behaviour judged to be incompatible with establishment of rapport or safe exposure to psilocybin
**Personal history**	Current or past history of bipolar I/II disorder, schizophrenia, schizoaffective disorder, psychotic disorder, or delusional disorder as assessed by a structured clinical interview (MINI) ≥ 1 suicide attempt in the past year requiring hospitalization, defined using the Columbia Suicide Severity Rating Scale (CSSRS) (Q6 (past year) = “y”) and clinical interview with a psychiatrist History of substance use and/or alcohol use disorder, of moderate severity or greater, in the past 12 months Lifetime history of substance use disorder with a hallucinogen Lifetime history of substance-induced psychosis Depression secondary to other medical conditions or bipolar I and II disorder
**Family history**	Family history of a first degree relative with a diagnosis of schizophrenia or a primary psychotic disorder and/or bipolar disorder
**Substance use**	Exposure to psilocybin or any other psychedelic in the past 12 months prior to screening and/or during the current MDE and use of psychedelics, such as ayahuasca/LSD, during the current depressive episode
**Diagnosis**	A clinical diagnosis of antisocial personality disorder and/or paranoid personality disorder (defined as meeting DSM-5.0 criteria) based on clinical interview and the MINI 7.0. Positive diagnoses on the MINI will be subject to confirmation at a clinical interview by a psychiatrist An active clinical diagnosis of borderline personality disorder as confirmed by the MINI 7.0 Diagnosis of any mild or major neurocognitive disorder meeting DSM-5 criteria and based on clinical interview/cognitive screening by a psychiatrist
**Other**	Current enrolment in an interventional study for depression or participation in such within 30 days of screening

## Assignment of interventions: Blinding

### Who will be blinded {17a}

This is a double-blinded study where neither the participant, their usual health care providers, nor the research team (including the QI/PI) will be explicitly aware of participants’ group assignment. Randomization is performed by a computer-generated sequence and both the psilocybin and placebo will be encapsulated and labelled in a double-blind manner with associated randomized codes.

### Procedure for unblinding if needed {17b}

In exceptional cases, the blind may be broken if the QI has deemed it medically necessary or if a data freeze has occurred based on the mutual discretion and agreement between PI and QI. In this instance, the QI and one SHSC staff representative (who is not involved in the trial in any capacity), will have access to the master key containing the blinded, unique bottle codes associated with a treatment and the unblinded participants’ data. Details pertaining to the unblinding that include the date and reason for unblinding will be documented in the CRF.

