### Concealment mechanism {16b}

The randomized 1:1 allocation sequence will be conducted using the Randomization Module in REDCap software. Each medication bottle label will contain a blinded, unique code that is associated with a specific treatment. Usona Institute will supply a master list containing the correspondence between the blinded, unique codes and their respective treatments. This list will be enclosed within an envelope and securely locked away, inaccessible to all study personnel.

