### Implementation {16c}

Participants will be enrolled by the Qualified Investigator upon meeting inclusion criteria (see Table 1) and providing their informed consent. Each bottle of drug product (containing one capsule per bottle) will be labelled by Usona Institute with a tear-away portion denoting the bottle and subject ID to facilitate randomization. The study coordinator will assign a unique identifier to each participant and provide an independent external assistant with subject IDs, bottle IDs, and tear-away portions for randomization. Random assignment to the treatment or control group will be conducted using a computer-generated sequence using REDCap, ensuring equal allocation. The independent external assistant, without involvement from study personnel, will generate the allocation sequence and create a master list of tear-aways concealed in an opaque envelope. Subsequently, the study coordinator will label each bottle according to the randomly assigned subject-bottle ID list.

**Table 1 Tab1:** Inclusion and exclusion criteria

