## Statistical methods

### Statistical methods for primary and secondary outcomes {20a}

The primary and secondary analyses will be conducted at Sunnybrook Health Sciences Centre, using open-source software tools, to the extent it is possible. Image processing will be conducted by a trained individual who will remain blind to the treatment allocation throughout the data analysis period. We propose to analyze our primary outcome using mixed-effects linear regression to measure CBF changes across our regions of interest from Baseline to Treatment Visit 1, as well as MADRS changes from Baseline, Week 3, and Week 6 following administration. A priori CBF regions consist of emotion regulation regions that are disrupted in MDD [109, 110], comprising the dorsolateral prefrontal cortex, salience network regions comprising the insula cortex, and default mode network comprising the parietal precuneus.

We will determine an optimal model for data analysis by fitting the model described in Eq. 1 to data using the *lme4* package in R, as well as additional models adding interaction effects of age, sex, and number of prior failed antidepressant treatments with drug to assess whether demographics or treatment-resistance modify the effect of psilocybin. An optimal model will be selected by comparing models fit by maximum likelihood estimation using a chi-squared test of model deviance. This will provide the added benefit of further robustness against the possibility of model non-convergence. As described in the sample size calculation, marginal means of a Visit x Drug interaction will be estimated using the *emmeans* package in R, and two within-subject contrasts of baseline to treatment visit 1 change in CBF will be calculated as well as a between-subject difference in these contrasts. Sidak’s correction for multiple comparisons will be applied to adjust *p*-values, with the primary outcome measure being the between-subject difference in the change in CBF attributable to psilocybin vs placebo at treatment visit 1.

For our exploratory analysis, peripheral levels of S100B, BDNF, and CRP will be measured using standard enzyme-linked immunosorbent assays or similar multiplexed immunoassay. All data analyses will be performed using SPSS 22.0. Multivariate linear regression analysis will be used to assess the relationship between baseline and change in peripheral biomarker measures and post-treatment change in MADRS scores.

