### Interim analyses {21b}

N/A. We do not have a planned interim analysis for this study.

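### The unblinding rule opens the full treatment key to the enrolling investigator, on medical need or at a data freeze that is not tied to the end of follow-up

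*Protocol article*

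**What the plan says.** Procedure for unblinding if needed {17b} is framed as a rule for exceptional cases and has two triggers. One is medical need as judged by the QI. The other applies "if a data freeze has occurred based on the mutual discretion and agreement between PI and QI". The same consequence follows from both: the QI and one hospital staff member uninvolved in the trial "will have access to the master key containing the blinded, unique bottle codes associated with a treatment and the unblinded participants’ data". The date and the reason are to be recorded in the case report form.

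Four other sections bear on this rule:

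- Concealment mechanism {16b}: the supplier's list linking bottle codes to treatments is "securely locked away, inaccessible to all study personnel".
- Who will be blinded {17a}: neither the participant, the usual care providers, "nor the research team (including the QI/PI) will be explicitly aware of participants’ group assignment".
- Implementation {16c}: "Participants will be enrolled by the Qualified Investigator upon meeting inclusion criteria".
- Interim analyses {21b}: "We do not have a planned interim analysis for this study".

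**The concern.** A rule that releases treatment codes should say when, to whom and how much. This one leaves two of the three too open.

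- **How much.** Medical unblinding normally needs one participant's code. Here even one medical case gives access to the master key. Nothing limits that access to the affected participant or to participants who have finished.
- **When.** The freeze has no date, no sample fraction and no link to the last visit. Recruitment is expected to run from August 2024 to August 2027 (Trial status), so there is ample time for a freeze before the end.
- **To whom.** The recipient is an active investigator. Besides enrolling, the QI confirms diagnoses and supervises medication tapering (Eligibility criteria {10}), may end a participant's involvement in some circumstances ({11b}) and reviews adverse events ({22}).

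If the QI holds the key while recruitment or dosing continues, decisions on whom to enrol, when to dose and whom to withdraw can be influenced by knowledge of the arm. No significance-level adjustment repairs that kind of bias.

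**Working it through.** **Sections side by side.**

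1. {16b} closes the code list to all study personnel. {17b} gives the QI the key on two triggers, one of them not medical. An unblinding procedure is by nature an exception to blinding, but {16b} names no exception, so the two need to be joined.
2. {17a} counts the QI and PI as blinded. Under {17b} the QI's blind can end, for every bottle code on the key, at a time that the PI and QI choose together.
3. The key links bottle codes to treatments. Under {16c} bottles are matched to participants through a subject-bottle list and labelled by the study coordinator. Someone with the key who can see a labelled bottle therefore knows that participant's arm before dosing. Group sizes are fixed ({16a}), so knowing past assignments also helps to predict the remaining ones. How far ahead the key reveals assignments depends on when subjects are matched to bottles. The article describes that timing in more than one way: enrolment triggers allocation in {10}, while randomization takes place at Treatment Visit 1 in {8}.
4. {21b} plans no interim analysis, and {17b} provides for no between-group test, stopping decision or claim at a freeze. These two sections are compatible if the freeze is the final lock.

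**Size of the hypothetical type I error effect.** The inputs from the article are alpha 0.05 on corrected p-values ({14}) and Sidak correction over the contrasts ({14}, {20a}), which are two within-drug contrasts and one between-group contrast. The assumptions, which are not in the article, are two-sided testing and one extra test at information fraction t whose result could be claimed.

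The overall error is P(|Z₁| > c or |Z₂| > c), where Z₁ and Z₂ are standard normal with correlation √t and the same critical value c applies at both looks.

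- Check with the single final test, c = 1.96: 5.0%, the nominal level.
- One extra look, c = 1.96: 8.9% at t = 0.3, **8.3% at t = 0.5**, 7.6% at t = 0.7. A simulation of two million runs gives 9.1% at t = 0.25, 8.3% at t = 0.5 and 7.3% at t = 0.75.
- Single CBF contrast at the Sidak level: 1 − (1 − 0.05)^(1/3) = 0.0170. One look gives 1.7%. Two looks, the first at half the data, give **2.9%**. The margin below 5% belongs to the family of three contrasts and is not spare for extra looks.
- Freeze defined as final lock: one look, so 5.0% and no inflation.

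The bias from an unblinded QI cannot be computed from anything in the document. The sample size calculation is not affected.

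**The case against.** A reader might infer that the protocol allows unblinded interim analyses without error control, and so contradicts its statement that none is planned. The document does not support that. A data freeze can mean the freeze at the end of data collection, and then {17b} and {21b} agree. No test is attached to the freeze. The 8.3% needs an invented look at an invented time whose result can be claimed, and it overstates the matter for the Sidak-adjusted CBF contrast. Nor does {17b} say that the PI receives the codes. It names the QI and one uninvolved staff member.

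There are also safeguards. The freeze needs agreement between PI and QI, and the unblinding is documented. Images are processed by someone "who will remain blind to the treatment allocation throughout the data analysis period", and CBF is an MRI measurement, less open to influence than a rating. Each participant's blinded period is about three weeks, because the second dose is open-label psilocybin for everyone. The article condenses a fuller protocol, which may define the freeze. The mention of unblinded participants' data can also be read as covering only those whose blind was broken.

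Most of this stands, and it removes the type I error claim as a main finding. It does not remove the operational point. The article does not merely omit a detail: it states a rule, and the rule gives the key without limiting it to one participant. Final unblinding after lock is routine, so placing the freeze among exceptional, discretionary events does not point clearly to final lock. Blinded image processing and an objective endpoint do not protect enrolment, withdrawal or the MADRS primary outcome. A short blinded period does not help participants who are not yet dosed.

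**Conclusion.** The point holds as one of concealment and operational bias. Followed as written, a single medical unblinding or an early freeze gives the enrolling investigator the whole key, including the codes of bottles not yet used. That fits poorly with {16b} and {17a}. It matters only if either trigger occurs before the last participant has finished, and its size cannot be estimated from the document.

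Inflated type I error is a possibility and not a property of the plan. It is about 8.3% for an endpoint tested at an unadjusted two-sided 5% with one extra claimable test at half the data, about 2.9% for one Sidak-adjusted CBF contrast under the same assumption, and none if the freeze is the final lock. The text permits an early look but does not plan one, and the no-interim statement is not contradicted.

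**What to change.** Change {17b} in three ways:

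1. For medical need, release only the affected participant's code and leave the rest of the key sealed.
2. Define the data freeze as database lock after the last participant's final follow-up, and open the full key only then. Otherwise delete that trigger.
3. Reconcile {16b} and {17a} with it: say who holds the list, and name single-participant medical unblinding as the only exception before lock.

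If an unblinded cumulative safety review is needed during the trial, route it to the independent medical monitors already appointed in {21a}, not to the QI.

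The cost is a few sentences and no change to sample size or analysis. The small downside is that the QI and PI lose the discretion to open the code early.

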## Data collection and management

### Plans for assessment and collection of outcomes {18a}

The assessments to be collected for both primary and secondary outcomes can be found in Table 2. For each participant, much of the data will be securely stored in the form of an electronic case report form (eCRF) which will include participant demographics, clinical scales and assessments, medical information including any pre-existing conditions and history, concomitant medications and therapies, vital signs (i.e., ECG, blood pressure), baseline blood tests, follow-up visits, any AEs or SAEs (if applicable), documentation of a participant’s informed consent, study visit dates, participant identification numbers, and any documentation pertaining to the appropriate data entry, management, validation, and archival. Paper-based copies of study questionnaires will be kept in the physical CRF with the unique, anonymized identification number assigned to a given participant and securely stored on-site in an area with restricted access at the hospital. Participant data captured during the trial will only be identified by a participant ID and managed in the electronic CRF (eCRF) that will be securely stored in online Research Electronic Data Capture (REDCap) software. REDCap is a secure, web-based software that is designed to support data capture for clinical trials and research studies. MRI data will be stored on a secure research server at Sunnybrook Health Sciences Centre. All questionnaires used in the study have been previously published and validated for research and/or clinical use. The ASL and MRI techniques have been previously published and validated.

**Table 2 Tab2:** Primary and secondary outcomes

**Primary outcomes**	• Significant alterations in regional CBF across three a priori brain regions from baseline to treatment visit 1
	• Improvement in depressive symptoms using the Montgomery-Asberg Depression Rating Scale (MADRS) from baseline to week 3 and week 6 following initial psilocybin/placebo administration. Higher scores with respect to the MADRS minimum (0) and maximum (60) values represent a worse treatment outcome [89]
**Secondary outcomes**	• Baseline grid-version of the 17-item Hamilton Depression Rating Scale (GRID-HAMD-17) score [Time Frame: Baseline]. The GRID-HAMD is a 17-item clinician-administered rating scale designed to assess severity of depressive symptoms. The score range is 0 to 52, with higher score indicating more severe depression [90]
	• Incidence of response [Time Frame: Up to study end point]. The proportion of participants with a response (defined as a ≥ 50% improvement in MADRS total score from Baseline) at week 3 post psilocybin administration. The minimum and maximum values are 0 and 60 and a higher score represents a worse outcome [91]
	• Incidence of remission [Time Frame: study endpoint]. The proportion of participants with remission (defined as MADRS total score < 11) at week 3 and 6 following the initial psilocybin/placebo administration. The minimum and maximum values are 0 and 60 and a higher score means a worse outcome [91, 92]
	• Patient Health Questionnaire 9-item (PHQ-9) [Time Frame: Baseline up to study end point/weeks]. The PHQ-9 is a self-rated measure of depressive symptom severity in the past two weeks. Each of the nine items is rated on a Likert scale, ranging from 0 (not at all) to 3 (nearly every day), and summed for a total score between 0 (no symptoms) to 27 (most severe) [93]
	• 16-item Quick Inventory of Depressive Symptomatology–Self-Report (QIDS-SR-16) [Time Frame: Baseline up to study end point/weeks]. The QIDS-SR-16 is a self-report scale with scores that range from 0 to 27. Higher scores indicate greater depression [94]
	• Clinical Global Impressions Scale (CGI) [Time Frame: Baseline up to study end point/weeks]. The CGI severity module assesses the severity of a person’s depressive illness using a seven-point Likert scale, ranging from “Normal, not at all depressed” to “Among the most extremely depressed patients”. The CGI improvement module evaluates the global improvement of a person’s condition since their last visit on a seven-point Likert scale, ranging from “Very much improved” to “Very much worse” [95]
	• Columbia Suicide Severity Rating Scale (CSSRS) [Time Frame: Baseline up to study end point /weeks] The CSSRS evaluates suicidal ideation and behaviour. The suicidal ideation score ranges from 0 (no ideation) to 5 (active suicidal ideation with specific plan and intent). Suicidal ideation intensity score ranges from 0 (no ideation) to 25 (most severe). The presence of suicidal behaviour is rated as a binary response; the lethality of previous actual attempts is rated on a scale of 0 (no or very minor physical damage) to 5 (death) and the potential lethality of actual attempts are rated on a scale of 0 (behaviour not likely to result in injury) to 2 (behaviour likely to result in death despite available medical care) [96]
	• Brief Psychiatric Rating Scale (BPRS) [Time Frame: Baseline up to study end point /weeks]. The BPRS rating scale has 18 items, each item rated on a severity scale of 1 (not present) to 7 (extremely severe). 0 is entered if the item is not assessed [97]
	• Sheehan Disability Scale (SDS) [Time Frame: Baseline up to study end point /weeks]. The SDS total score ranges from 0 to 30 with 0 representing no impairment and 30 representing severe impairment. The last two items of the scale (Days Lost and Days Unproductive) range from 0 to 7 (higher number denotes greater impairment) [98]
	• World Health Organization-5 Well-Being Index (WHO-5) [Time Frame: Baseline up to study end point/weeks]. The WHO-5 is a measure of overall well-being, rated on a scale of 0 to 25, with higher scores denoting higher quality of life [99]
	• World Health Organization Disability Assessment Schedule 2.0 (WHODAS 2.0) [Time Frame: Baseline up to study end point/weeks]. The WHODAS 2.0 is a self-reported disability questionnaire based on the International Classification of Functioning, Disability, and Health (ICF). It includes 36 questions, organized under six domains (cognition, mobility, self-care, getting along, life activities and participation). Each question must be answered based on the perceived difficulty for performing activities using a 5-point scale (none, mild, moderate, severe, and extreme) [100]
	• Generalized Anxiety Disorder-7 (GAD-7) [Time Frame: Baseline up to study end point/weeks]. Total score ranges from 0 to 21; a higher score denotes greater symptom severity [101]
	• Snaith-Hamilton Pleasure Scale (SHAPS) [Time Frame: Baseline up to study end point/weeks]. The SHAPS total score ranges from 14 to 56, wherein a higher score indicates greater hedonic capacity (lower anhedonic severity) [102]
	• 6-Item Clinician Administered Dissociative Symptom Scale (CADSS-6) [Time Frame: Treatment visit 1 up to study end point/weeks]. Total scores range from 0 to 16, wherein a higher score indicates greater dissociation [103]
	• Stanford Expectations of Treatment Scale (SETS) [Time Frame: Baseline] This scale contains six items measuring positive (3 items) and negative (3 items) treatment expectancies. Each of the six items is coded with a similar 7-point scale starting from “strongly disagree” to “strongly agree” [104]
	• Montreal Cognitive Assessment (MoCA) total score [Time Frame: Baseline up to study end point]. Cognitive Screening assessment tool [105]
	• We will use the CANTAB software program for evaluating cognitive domains. [Time Frame: Baseline up to study endpoint]. Domains to be assessed: Sustained attention (Rapid Visual Information Processing), Psychomotor speed (Reaction Time), Executive function (Spatial Working Memory, One Touch Stockings of Cambridge), Memory (Delayed Matching to Sample, Paired-associates learning), and Emotional cognition (Emotion Recognition Task) [106]
	• Hopkins Verbal Learning Test-Revised (HVLT-R) Total Score [Time Frame: Baseline up to study endpoint]. A list learning test that contains 12 nouns that are read to a participant for three consecutive trials. After each trial, a participant is asked to recall the words that were read to them. The number of words recalled on each trial is summed together to produce a total score. The higher total score equates to a better outcome [107]
	• Revised Mystical Experience Questionnaire (MEQ) [Time Frame: 6–8 h post-treatment, the day after treatment, and at Final follow-up]. A validated self-report revised 30-item questionnaire recording elements that comprise the mystical experience [108]
	• Persistent Effects Questionnaire (PEQ) [Time Frame: Final follow-up]. A non-validated self-report 145-item questionnaire that describe any changes in the participants’ lives that may be attributed to the psilocybin treatment [108]

